## Study stopping rules

The overall study will be paused, and appropriate authorities (e.g., IRB, Knight Data and Safety Monitoring Committee) notified if the following events occur:

• Life-threatening grade 4 toxicity attributable to protocol therapy that is unmanageable, or unexpected.

• Death suspected to be related to ICG injection.

• As indicated by statistical stopping rules in this protocol.

- - 1. Baseline Descriptive Statistics

Summaries of patient demographics, baseline characteristics and baseline disease characteristics will be presented for participants using the safety evaluable population to include the following:

1. Demographics: Sex; Age; Ethnicity; Race; Region of subsite
2. Baseline characteristics: Height (cm); Weight (kg); ECOG performance status
3. Baseline disease characteristics: Disease stage at study entry; cancer therapy; biomarker status

## Handling of Missing Data

Patient and intervention data will be carefully recorded. In the event that a specific data point could not be recorded, no input or analysis will be done with missing data. Missing data will be reported as such and if esencial information is not found, participant may be excluded entirely or partially from the study.

# CLINICAL MONITORING

## OHSU Knight Cancer Institute Data & Safety Monitoring Plan

All clinical trials at the Knight are required to have Data and Safety Monitoring Plan (DSMP). This study is under the oversight of the Knight Cancer Institute’s DSMC as described in the Knight institutional DSMP. The Knight DSMP outlines the elements required to ensure the safety of clinical trial participants, the accuracy and integrity of the data, and the appropriate modification of cancer-related clinical trials for which significant benefits or risks have been discovered or when the clinical trial cannot be successfully concluded. The Knight DSMP also describes the methods and procedures for ensuring adequate, risk-based oversight of cancer-related research at OHSU.

As described in the Knight DSMP, regardless of a trial’s risk level and any specific Knight oversight in place, the Investigator is singularly responsible for overseeing every aspect of the design, conduct, and final analysis of his/her investigation.

The Knight DSMC reviews and monitors study progress, toxicity, safety, and other data for this study. The DSMC will address any issue that raises questions about data integrity or trial participant safety with the Investigator and study team. Should any major concern arise, the Knight DSMC may recommend corrective action, and determine whether to suspend or terminate the study.

## Clinical Data & Safety Monitoring

As part of the Quality Assurance plan and in full agreement with NIH policy (NIH Guide, NIH Policy for Data and Safety Monitoring, June 10, 1998) that states all clinical trials require monitoring to ensure the safety of study participants and the validity and integrity of the data, monitoring will be a continuous, ongoing and multifaceted process. This includes external review by the DSMC and IRB(s), as well as internal data quality control, review and evaluation. Site monitoring visits are central to this process, and will include reporting to appropriate individuals with oversight responsibilities.

The OHSU Investigator is ultimately, singularly responsible for overseeing every aspect of the investigation, including design, governing conduct at all sub-sites, and final analysis of study data.

In the absence of a formal monitoring plan, the Investigator may work with his/her study team to conduct and document internal monitoring of the study to verify protection of human participants, quality of data, and/or ongoing compliance with the protocol and applicable regulatory requirements.

If at any time Investigator noncompliance is discovered at OHSU or any sub-site, the Investigator shall promptly either secure compliance or end the Investigator’s participation in the study.

Independent audits will be conducted by the Knight DSMC to verify that the rights and well-being of human participants are protected, that the reported trial data are accurate, that the conduct of the trial is in compliance with the protocol and applicable regulatory requirements, and that evidence of ongoing investigator oversight is present.

## Quality Assurance & Quality Control

The investigational site will provide direct access to all trial-related source data/documents and reports for monitoring by the monitor and/or sponsor, and auditing by the Knight DSMC and/or regulatory authorities.

All Knight Cancer Institute clinical trials must have a Data and Safety Monitoring Plan (DSMP). All clinical work conducted under this protocol is subject to ICH GCP guidelines. This includes inspection of study-related records by the lead site, Sponsor, its designee, or health authority representatives at any time.

QA audit activities will occur as detailed in the Knight’s institutional DSMP. All discrepancies, queries, deviations, observations, and findings of non-compliance will be compiled into a final audit report. The PI must review and assess each finding and generate a response to the audit report that incorporates Corrective and Preventative Action (CAPA). A CAPA must approach analyzing root cause(s) of noncompliance in order to identify and determine changes to correct and resolve issues and prevent recurrence.

Quality Control (QC) activities will occur to monitor and ensure the safety of study participants and the validity and integrity of data. Monitoring will be a continuous, ongoing, and multifaceted process. This includes review by the Knight DSMC and applicable IRB(s), as well as internal data quality control, review and evaluation. Site monitoring visits are central to this process and will include reporting to appropriate individuals with oversight responsibilities.

The Sponsor-Investigator, or study monitor, will verify that the clinical trial is conducted, and data are generated, documented (recorded), and reported in compliance with the protocol, GCP, and the applicable regulatory requirements (e.g., Good Laboratory Practices (GLP), Good Manufacturing Practices (GMP)).

# SUPPORTING DOCUMENTATION AND OPERATIONAL CONSIDERATIONS

## Source Data/Documents

The Investigator is responsible for ensuring the accuracy, completeness, legibility, and timeliness of the data reported. All source documents should be completed in a neat, legible manner to ensure accurate interpretation of data. The Investigator will maintain adequate case histories of study participants, including accurate CRFs, electronic (e)CRFs and relevant electronic data capture (EDC) system (if applicable), and all relevant source documentation.

- - 1. Participant & Data Confidentiality

The information obtained during this clinical study is confidential, and unless otherwise noted, disclosure to third parties is prohibited. Information contained within this study will be maintained in accordance with applicable laws protecting participant privacy, including the provisions of the Health Insurance Portability and Accountability Act (HIPAA).

Participant confidentiality is strictly held in trust by the site Investigator(s) and study team. This confidentiality is extended to cover testing of biological samples and genetic tests and the clinical information about participants. Therefore, the study protocol, documentation, data, and all other information generated will be held in strict confidence. No information concerning the study, or the data will be released to any unauthorized third party without prior written approval of the sponsor.

The study monitor, other authorized representatives of the sponsor, representatives of the IRB or manufacturer supplying study product may inspect all documents and records required to be maintained by the Investigator, including but not limited to, medical records (office, clinic, or hospital) and pharmacy records for the participants in this study. The clinical study site will permit access to such records.

The study participant’s contact information will be securely stored at each clinical site for internal use during the study. At the end of the study, all records will continue to be kept in a secure location for as long a period as dictated by local IRB and institutional regulations. Study participant research data, which is for purposes of statistical analysis and scientific reporting, will be transmitted to and stored within the Knight Cancer Institute per [OHSU’s Information Security Directives](http://www.ohsu.edu/xd/about/services/integrity/policies/ips-policies-by-category.cfm). Individual participants and their research data will be identified by a unique study identification number. The study data entry and study management systems used by clinical sites and by Knight Cancer Institute research staff will be secured and password protected per [OHSU’s Information Security Directives](http://www.ohsu.edu/xd/about/services/integrity/policies/ips-policies-by-category.cfm). At the end of the study, or after the appropriate period of record retention stated in Section 13.1.4, all study databases will be de-identified and archived within the Knight Cancer Institute.

- - 1. Data Collection & Storage: Privacy, Confidentiality & Security

Data collection is the responsibility of the clinical trial staff at the site under the supervision of the site Investigator. The Investigator is responsible for ensuring the accuracy, completeness, legibility, and timeliness of the data reported. Standard institutional practices will be followed as described in the [OHSU’s Information Security Directives](http://www.ohsu.edu/xd/about/services/integrity/policies/ips-policies-by-category.cfm) to maintain the confidentiality and security of data collected in this study. Study staff will be trained on these procedures.

Loss of participant confidentiality is a risk of participation. Efforts will be made to keep study participant identities confidential except as required by law. Participants’ samples will be identified by code only. Specifically, each consenting participant will be assigned a unique coded identifier consisting of numbers. This identifier will be associated with the participant throughout their participation in the trial. The coded identifier will also be used to identify any participant specific samples.

Basic accrual tracking information (demographic, consent, visit information) will be captured in OHSU’s electronic clinical research information system (eCRIS), hosted on OHSU secure servers, and managed by OHSU’s information technology group at their data center in downtown Portland, Oregon. Any additional printed documents containing participant identifiers, such as those from the medical record to confirm eligibility, will be filed in binders and kept in a locked, secure location.

Study outcome data will be captured in electronic case report forms (eCRFs) using an electronic data capture (EDC) system approved by OHSU’s office of Information Privacy and Security. To preserve confidentiality, PHI in the EDC system will be limited to just birth date and visit dates. The web-accessible EDC system is password protected and encrypted with role-based security and administered by designated informatics staff within OHSU or Knight Cancer Institute. All users of the database are assigned a unique ID, username, and password and must complete training appropriate to their role before they are authorized to enter, access, and store data in the database.

Where applicable, data from correlative studies may be entered into the EDC system by study personnel. All other electronic data extracts will be stored only on local study site computers and restricted drives, which are limited to only study investigators and staff with authorization to access the data. Quality assurance will be conducted as outlined in Section 12.3, Quality Assurance & Quality Control

*13.1.3 National Surgical Quality Improvement Project (NSQIP) & Efficacy Data Collection*

NSQIP is an international initiative sponsored by the American College of Surgeons that records patient demographics, treatment regarding surgical interventions, and captures 30-day postoperative complications data. “Procedure-targeting” allows institutions to capture 100% of certain surgical procedures along with an expanded set of procedure-specific datapoints. OHSU has been procedure-targeting pancreatectomies for a decade.

Data collection for 30-day postoperative complications, including rates of fistula formation, will be performed by a trained NSQIP surgical clinical reviewer. Due to the workflow of NSQIP reviewers, a lag period between surgery is anticipated equaling up to 3-months. For the interim efficacy analysis, subject charts may be reviewed for information relevant to the primary endpoint by individuals other than the NSQIP reviewer. Data obtained from the NSQIP reviewer relating to primary or secondary endpoints will be separately reviewed by a member of the study team and any conflicts or discrepancies resolved. Finalized data will be entered into the EDC system and used for final analysis.

- - 1. Future Use of Stored Specimens and Data

With patient’s and IRB approval, tissue samples from the pancreas will be stored within the Oregon Pancreas Tissue Registry IRB00003609. Consent for aforementioned IRB is separate from this study (25055). Collection of blood could also be performed for further studies. These samples are used to better understand pancreatic pathologies and their complications. Consent of tissue storage can be withdrawn at any time by patients.

- - 1. Maintenance of Records

Records and documents pertaining to the conduct of this study, source documents, consent forms, laboratory test results and medication inventory records, must be retained by the Investigator for a period of 2 years following the date a marketing application is approved for the drug for the indication for which it is being investigated; or, if no application is to be filed or if the application is not approved for such indicate, until 2 years after the investigation is discontinued and FDA is notified. It is the responsibility of the sponsor to inform the Investigator when these documents no longer need to be retained.

If the Investigator relocates or for any reason withdraws from the study, the study records must be transferred to an agreed upon designee, such as another institution or another investigator at OHSU. Records must be maintained according to institutional or FDA requirements.

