# STUDY DESIGN

## Description of the Study Design

*Refer to* Section 11*, Statistical Analysis for additional information regarding statistical methods used in this study.*

This is a Phase II study to assess diagnostic parameters of hypoperfused pancreatic cut edge via ICG and its relation to fistula formation versus conventional measurements. The study design consists of a single arm intervention group (n=50).

The trial will commence with the enrollment of the fifteen patients, after these 15 casesa logistics run-in of the OR ICG technique and timing will be done. During the logistics run-in, the PI will evaluate team satisfaction and measurement outcomes. This will be done through the application of a 3-question paper-based quality survey, attached in the supporting documents for the protocol. If an average score below 50% is given, study will be terminated to avoid negative impact on the logistics of pancreatectomies. Survey scores are calculated depending on the answer given, A= 0% B = 16.5% C = 33%. Minimum score 0 maximum score 100. Progressive study enrollment will continue throughout the adjustments, and enrollment will be halted if any major concerns arise. If the interim analysis does not result in study termination, enrollment of the remaining participants will resume to enroll a total of 50 patients completing study intervention and follow-up.

Aside from interim analysis evaluating logistics. A patient safety analysis will be performed at the same time. Herein, potential factors of the clinical trial that could negatively impact patient outcomes will be addressed. These factors include adverse effects of ICG administration and factors from the clinical trial process that negatively impact the conventional treatment course of patients. If any concerns are identified on interim safety analysis, the study could temporarily pause enrollment until the issues are addressed. This is to supplement study stopping rules delineated in 9.6 and Data and Safety forms.

The study schedule will be divided into 2 periods: (1) the intra-surgical period which starts at the time of ICG injection and ends when the surgical procedure is terminated and (2) the postoperative period which begins at the end of surgery and ends 30 days postoperatively.

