## Study Discontinuation and Closure

This study may be temporarily suspended or prematurely terminated if there is sufficient reasonable cause. Written notification that documents the reason for study suspension or termination will be provided by the suspending or terminating party to OHSU Coordinating Center, local IRB, and other regulatory authority (if required). If the study is prematurely terminated or suspended, the Investigator must promptly inform the IRB and provide the reason(s) for the termination or suspension. The OHSU Coordinating Center will notify sub-site(s) of any study suspension or discontinuation.

Reasons for terminating the study may include the following:

• Unfavorable assessment of risk/benefit ratio

• Incidence or severity of adverse events, in this or other studies, that indicates a

potential health hazard to participants

• Demonstration of lack of efficacy that warrants stopping

• Data that are not sufficiently complete and/or evaluable

• Investigator not adhering to the study protocol or applicable regulatory guidelines in conducting the study

• Participant enrollment is unsatisfactory

• Submission of knowingly false information from the study site to OHSU Coordinating Center or regulatory authority

• Upon instruction by local or other regulatory or oversight authority.

The study may resume once concerns about safety, protocol compliance, and/or data quality are addressed as applicable and requirements of the OHSU Coordinating Center, funder, IRB and/or other applicable regulatory authority are satisfied.

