## Study Stopping Rules

The overall study will be paused, and appropriate authorities (e.g., IRB, Knight Data and Safety Monitoring Committee) notified if the following events occur:

• Life-threatening grade 4 toxicity attributable to protocol therapy that is unmanageable, or unexpected.

• Death suspected to be related to ICG injection.

• As indicated by statistical stopping rules in this protocol.

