## Description of Statistical Methods

- - 1. General Approach

Descriptive statistics will be used to summarize patients’ baseline characteristics and baseline disease characteristics. This information will be presented with percentages, means with standard deviations median and range as suitable. Inferential tests will use a null-hypothesis significance testing of <0.05.

- - 1. Analysis of Primary Endpoint(s)

*11.4.2 Primary endpoint – Leak rate*

We will assess the association between ICG perfusion and leaks using a chi-square test. Logistic regression analysis will be further utilized to evaluate covariates influencing the presence/absence of leaks, with specific attention to the predictive value of percent maximum perfusion metrics and time to maximum metrics at the set timepoints in the protocol. Refer to Sections 3.1 for additional information

- - 1. Analysis Of The Secondary Endpoint(S)

*11.4.3.1 Secondary endpoint –*

We will use descriptive statistics to summerize the grade of leasks and ICG metrics.

*11.4.3.2 Secondary endpoint – ICG logistics*

The results of the survey to be applied to surgeons and other OR staff will be summerized using a descriptive statistics.

- - 1. Safety Analyses

Adverse events will be tabulated by the Medical Dictionary for Regulatory Activities (MedDRA Version 21.1) preferred term and system organ class. The severity of the AE will be assessed by National Cancer Institute (NCI) Common Terminology Criteria for Adverse Events (CTCAE) version 5.0. Using the safety analysis set, descriptive statistics will be used to summarize all on-study AEs, grade 3-4 AEs, treatment-related AEs, grade 3-4 treatment-related AEs, SAEs, treatment-related SAEs, and AEs leading to study therapy discontinuation. Grade 3-4 laboratory abnormalities will be summarized using worst grade NCI CTCAE v5.0 criteria.

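### The protocol refers to an interim efficacy analysis and to statistical stopping rules that it never defines, and it does not require those who read or resolve leak status to be masked to ICG results.

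*Protocol*

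**What the plan says.** Section 13.1.3, which describes how 30-day outcomes are collected, allows for a reviewer lag of up to three months and then says: "For the interim efficacy analysis, subject charts may be reviewed for information relevant to the primary endpoint by individuals other than the NSQIP reviewer". Of the reviewer's endpoint data it says that they "will be separately reviewed by a member of the study team and any conflicts or discrepancies resolved" before the final analysis.

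Description of the Study Design sets out one interim, after 15 cases. It has a numeric rule on a staff survey: "If an average score below 50% is given, study will be terminated to avoid negative impact on the logistics of pancreatectomies". A safety review goes with it: "A patient safety analysis will be performed at the same time". Neither concerns leak by perfusion group.

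Study Stopping Rules (9.6) lists a final trigger for pausing the study: "As indicated by statistical stopping rules in this protocol". The synopsis carries the same pointer, and so does the list repeated inside the statistics chapter. Study Discontinuation and Closure includes, among possible reasons to terminate, "Demonstration of lack of efficacy that warrants stopping", without a criterion.

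The statistics chapter plans a chi-square test of leak against perfusion, with logistic regression to follow, and sets one level: "Inferential tests will use a null-hypothesis significance testing of <0.05".

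Under Measures to Minimize Bias, surgeons are blinded to the perfusion measurements and the images are kept from people outside the study. Study personnel acquire and analyse them.

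**The concern.** An efficacy look that is named but not defined leaves open when the primary endpoint is examined by perfusion group, by whom, and what may follow. If it can lead to a claim of association, an unadjusted 0.05 at the final test no longer holds the overall error at 5%. If it can lead to stopping for lack of association, power is lost. In either case the emerging relation between perfusion and leak becomes known to a team that is still collecting data.

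The stopping-rule pointer has a practical consequence too. An ethics board or monitoring committee told to pause the study on a statistical rule cannot do so if no rule is written.

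The masking gap matters because the protocol itself treats knowledge of the perfusion result as a threat: it excludes from analysis any case in which the surgeon may have seen the measurement. The people who read charts for the endpoint and settle disagreements about it are under no corresponding requirement.

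**Working it through.** **Side-by-side reading**

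| Item | Where it is referred to | Where it is defined |
| --- | --- | --- |
| Interim on logistics | Study design section | Same section: after 15 cases, terminate if average survey score is below 50% |
| Interim on safety | Study design section | Same section: same time as logistics, no numeric threshold |
| Interim on efficacy | 13.1.3 only | Nowhere: no timing, test, boundary or decision |
| Statistical stopping rules | Synopsis, 9.6, statistics chapter | Nowhere: the entry in the statistics chapter only repeats the pointer |
| Masking of surgeons | Measures to Minimize Bias | Same section |
| Masking of chart readers and discrepancy resolver | Not mentioned | Nowhere |

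**Effect on type I error, if the look could declare success**

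Inputs from the protocol: N = 50 and significance level 0.05. Assumptions, since the protocol states none of these: two-sided testing; one efficacy look, at 15 patients (borrowed from the only interim described) or at 25 (half); success declared at 0.05 at either analysis.

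With a single final test, the error is P(|Z| > 1.96) = 0.05, which is the protocol's figure.

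With one look added, the interim and final statistics are approximately bivariate normal with correlation √t, where t is the fraction of patients at the look. The overall error is

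1 − P(|Z₁| ≤ 1.96 and |Z₂| ≤ 1.96).

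- Look at 15: t = 15/50 = 0.30, correlation 0.548, overall error 1 − 0.9107 = 0.0893.
- Look at 25: t = 25/50 = 0.50, correlation 0.707, overall error 1 − 0.9169 = 0.0831.

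Simulating the chi-square test itself (400,000 runs, common leak rate 20% to 32.5%, patients equally likely to fall in either perfusion group) gives 7.9% to 8.7% for the look at 15 and 8.3% to 8.8% for the look at 25. The normal approximation is adequate.

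**How little a 15-patient look could show**

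From the sample-size section: 20% leak with normal perfusion, a 25-point difference (hence 45%, reading the difference as absolute) and balanced groups (7.5 each). Pooled rate p̄ = 0.325.

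Power = Φ{[0.25 − 1.96·√(2 × 0.325 × 0.675/7.5)] / √[(0.20 × 0.80 + 0.45 × 0.55)/7.5]}
= Φ{(0.25 − 0.474)/0.233} = Φ(−0.96) ≈ 0.17.

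If a look were taken there, it would have about 17% power at the two-sided 0.05 level.

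**The case against.** The strongest reply is that these phrases are drafting residue in a small study meant to gather preliminary data, and that no one intends an efficacy look. That may be so. It does not settle the matter, because the text gives the look an operational purpose (who may read charts for it) and because the pointer says that the rules stand in this protocol. A separate analysis plan would not cure either.

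Several stronger readings are tempting and are not supported.

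- *That the endpoint readers are unblinded.* The protocol does not say so. It leaves them outside its masking provisions, and study personnel handle the images. The supportable statement is that masking is not required of them.
- *That keeping 0.05 is an error in itself.* It is one only if a look can end in a positive claim, and no section allows that. The only efficacy-related stop named is for lack of efficacy, which does not raise type I error.
- *That an efficacy look is planned at 15 patients.* The 15-case review is assigned to logistics and safety, and the efficacy look has no stated timing.
- *That a futility stop would end a truly positive study with a known probability.* One can compute the chance that 15 patients show no difference or a reversed one under 20% versus 45%. It is 12.1% with 8 normal and 7 reduced, but 16.6% with 7 and 8. Both the rule and the split are invented, so neither figure describes this plan.
- *That subjective grading threatens the primary test.* The judgement about a change in management separates Grade B from a biochemical leak. Grade is a secondary endpoint, summarised descriptively. For the primary endpoint, a drain amylase above three times the upper limit is sufficient by itself. Some judgement remains, since the disease-evaluation section also relies on clinical suspicion, but the exposure is smaller than for grade.

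Two further points stand. The lack-of-efficacy item belongs to a general list of possible reasons for closure and is not an interim mechanism. The stopping-rule pointer in 9.6 sits among safety triggers and should not be read as an efficacy boundary.

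**Conclusion.** The protocol contradicts itself. It refers to an interim analysis of the primary endpoint and to statistical stopping rules, while its design section describes only a logistics and safety interim and its statistics chapter contains no efficacy look, boundary, stopping rule or adjustment. This rests on the text alone.

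The size is conditional. With one unadjusted look that can declare success, overall two-sided error is about 8 to 9% instead of 5%. With a futility-only look there is no inflation but a possible loss of power. With no look at all, 0.05 stands as written.

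The masking gap is an omission by a protocol that otherwise takes masking seriously, and is not evidence that anyone is unblinded. It bears mainly on leak grade and, to a lesser degree, on leak status. The point should be corrected, and the correction is cheap.

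**What to change.** 1. In 13.1.3, remove the reference to an interim efficacy analysis. In the design section, state that the 15-case review covers logistics and safety only and that leak by perfusion is not examined before the final analysis at 0.05. If a look is intended, define its timing, test, boundary and alpha instead. For equal two-sided levels at both analyses, holding 5% overall would need about 0.027 at each with the look at 15 patients, or 0.029 with the look at 25.
2. Reconcile the stopping-rule pointer in the synopsis, 9.6 and the statistics chapter: either write the rule or remove the pointer. The general lack-of-efficacy item in the closure section can stay.
3. Require that the existing team member who reads or resolves leak status and grade did not acquire the ICG data and cannot see them.

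The cost is wording and one role assignment among existing staff. No patients, visits or measurements are added.
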